### Sampling and Sample Size

Using the sputum biomarkers to predict exacerbations, we based the sample size on the difference in exacerbation frequency in time periods when an exacerbation was predicted compared to time periods when no exacerbation was predicted. This will give an odds ratio of exacerbation following detection of sputum biomarkers.

Time periods will consist of approximately 10 days, of which it will be estimated that there may be on average 12 per participant (assuming an average of 4 months of follow-up). It is estimated that an exacerbation will occur in 60% of time periods in which it is predicted and 10% of time periods in which it is not predicted. It is also assumed that a predicted exacerbation will be made in only 1 in 12 time points (8% of all time points). Using a 5% significance level and 90% power, it is calculated a total of 120 time periods will be required.

However, as there are multiple time periods from the same participant, the data values are unlikely to be independent of each other and thus the sample size requires inflating. Assuming intraclass correlation of 0.18, a design effect of approximately 3 is calculated. This implies that 360 time periods are required for the analysis. This equates to a total of 30 participants for the study. The proposed 30 participants will consist of 20 participants with chronic *P aeruginosa* infection (10 with primarily COPD and 10 with NCFB) and 10 participants with *H influenzae* infection.

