#### Analysis of Endpoints

The first stage of the data analysis is to use data on the collected parameters (eg, peak flow, pulse rate, oxygen saturation, activity data) to predict when an exacerbation is likely. Control charts will be used to determine the boundaries of normal behavior for each parameter. Separate control charts will be used for each participant, as what constitutes normal behavior will vary from participant to participant. When a parameter strays from normal behavior (eg, exceeds 99% control limits), an exacerbation will be predicted.

To examine the association between predicted exacerbation and actual exacerbation, participant follow-up will be divided into periods of time (eg, 7-10 days). A comparison of actual exacerbation when exacerbation has and has not been predicted will be made. To allow for the repeat measurements over time from the same participants, the analysis will be performed using multilevel logistic regression. Additionally, the sensitivity and positive predictive value of the predictions will also be calculated. Estimated values will be presented along with corresponding confidence intervals. Further exploratory analysis using novel computing methods will be conducted.

Health care use data will be presented descriptively (eg, the frequency and type of health care contacts over the study period for different participant groups).

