#### Procedure for Dealing with Missing, Unused, and Spurious Data

The primary analysis will be restricted to collected data only, without any data imputation. The distributions of the parameters collected will be assessed, and implausible values may be excluded from the analysis. Any data exclusions will be justified both clinically and statistically.

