## Discussion

The SENSOR study will provide a prospective evaluation of the efficacy of this home self-monitoring system in people with chronic airway infection. The data collected will allow us to determine the key elements of the self-monitoring system for prediction of exacerbations in order to reduce the burden on monitoring on patients in future.

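### Prediction rules are developed and scored on the same 30 participants with no validation step, so sensitivity and PPV are apparent values and do not amount to a prospective evaluation of the system

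*Protocol article*

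**What the plan says.** The Primary Objective and the Methods Overview make model development the purpose of the six-month data. Description of Analysis Populations puts every recruited participant into one analysis set.

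Under Analysis of Endpoints, "Control charts will be used to determine the boundaries of normal behavior for each parameter", with separate charts for each participant. A parameter outside its limits counts as a predicted exacerbation. Follow-up is then cut into periods, and predicted and actual exacerbations are compared by multilevel logistic regression. "Additionally, the sensitivity and positive predictive value of the predictions will also be calculated". The 99% limit, the 7 to 10 day period and the list of parameters are all given as examples. Exploratory modelling of an unspecified kind follows.

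The section on missing and spurious data adds that "The distributions of the parameters collected will be assessed, and implausible values may be excluded from the analysis", and requires any exclusion to be justified on clinical and statistical grounds.

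The Discussion states: "The SENSOR study will provide a prospective evaluation of the efficacy of this home self-monitoring system". It adds that the data will show which elements of the system matter for prediction, so that the monitoring burden can be reduced later.

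**The concern.** There is one cohort and one set of exacerbations. The rule (which parameters, how wide the limits, how long the window) is left open, and the data that would settle it are the data that score it. Nothing in the stated analysis separates the two: no held-out participants, no later test period, no resampling, no optimism correction. Sensitivity and PPV obtained this way describe fit to the development data. They do not estimate how the system would perform in a new patient, or in the same patient's next month.

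A second gap concerns the limits. The text does not say which days define normal behaviour. A device in use can only apply limits from earlier readings, and stable-state limits should not contain exacerbation days. Depending on that choice, the same data can give very different performance.

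At stake are the decision on which measurements to drop and the performance figures that readers would carry forward to the later large trial foreseen in the rationale section.

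**Working it through.** **1. The plan's own sample size.** Inputs from Sampling and Sample Size:
- Event rates: "an exacerbation will occur in 60% of time periods in which it is predicted and 10% of time periods in which it is not predicted".
- One period in 12 flagged, so k = 11 unflagged periods per flagged period.
- "Using a 5% significance level and 90% power, it is calculated a total of 120 time periods will be required".

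Pooled rate p̄ = (0.6 + 11 × 0.1)/12 = 0.1417. Two-sided test of two proportions:

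n = [1.96·√(p̄(1−p̄)(1+1/11)) + 1.2816·√(0.24 + 0.09/11)]² / 0.5² = 7.31 flagged periods.

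With continuity correction this is 9.37, rounded up to 10. Then 10 + 110 = 120, which matches. Design effect 1 + 11 × 0.18 = 2.98; 120 × 2.98 = 357.6, about 360; 360/12 = 30 participants. The figures reproduce. They size an association test for a rule treated as already fixed, and allow nothing for developing or validating the rule.

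**2. What the planning figures imply.** Of 360 periods, 30 are flagged and 360 × 0.1417 = 51 contain an exacerbation. True positives are 30 × 0.6 = 18, so PPV is 60% and sensitivity is 18/51 = 35%.

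**3. Optimism from choosing a rule on the scored data.** Suppose no rule carries any signal. With 30 flags placed at random among 360 independent periods holding 51 events, the true-positive count X is hypergeometric with mean 30 × 51/360 = 4.25. For the best of K independent rules, E[max] = Σ(1 − F(x)^K), summed over x = 0, 1, …, where F is the distribution function of X.

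| K rules tried | Expected best true positives | Apparent PPV | Apparent sensitivity |
|---|---|---|---|
| 1 (the truth) | 4.25 | 14.2% | 8.3% |
| 5 | 6.43 | 21.4% | 12.6% |
| 10 | 7.20 | 24.0% | 14.1% |
| 20 | 7.88 | 26.3% | 15.5% |
| 50 | 8.70 | 29.0% | 17.1% |

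Real candidate rules overlap, so the inflation for a given K would be smaller than shown. The number of rules that will be tried is not known.

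**4. Sensitivity to the reference period.** This was simulated under assumptions that are not in the document: independent normal daily readings over 180 days, exacerbations at 14.2% per 10 days, a 14-day shift starting 3 days before treatment, 99% limits from the ordinary standard deviation, 10-day scoring, and a first 28 days free of exacerbation. Entries are sensitivity / PPV.

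| Parameters, shift when ill | Whole record, ill days in | Whole record, ill days out | First 28 clean days, scored later |
|---|---|---|---|
| 1, 1.5 SD | 0.15 / 0.28 | 0.40 / 0.38 | 0.44 / 0.29 |
| 1, 2.5 SD | 0.28 / 0.58 | 0.85 / 0.55 | 0.84 / 0.42 |
| 8, 1.5 SD | 0.73 / 0.23 | 0.99 / 0.21 | 0.99 / 0.16 |
| 8, 2.5 SD | 0.81 / 0.38 | 1.00 / 0.20 | 1.00 / 0.16 |

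Ill days in the limits lower sensitivity in every row, and PPV can look better or worse. Limits from only 28 days are less precise and give more false flags than limits from all stable days.

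**5. Periods left after a 28-day baseline.** The plan assumes 4 months on average, that is 12 periods of 10 days. Then (120 − 28)/10 = 9.2 periods each, and 30 × 9.2 = 276. The plan's own method then needs 120 × (1 + 8.2 × 0.18) = 120 × 2.476 = 297. At 14.2% per 10 days, the chance of an exacerbation within 28 days is 1 − (1 − 0.1417)^2.8 = 35%, assuming independence.

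**The case against.** Several objections carry weight.

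- **Limits set without outcomes do not overfit.** A control chart uses only the participant's own readings. This stands: optimism comes from choosing among rules and from fitted models, not from the charts themselves.
- **A reader might infer that the limits are built from the whole record, ill days included.** The text does not say so. It names no reference period, and its reference to normal behaviour fits a stable baseline at least as well. The statistical analysis plan, which is not shown, may settle this. Only the silence and its possible consequences can be raised.
- **A reader might infer that the exclusion rule will strip out the readings that raise an alarm.** The section covers implausible values only and asks for clinical and statistical justification. What remains is a matter of timing: nothing says that the exclusions precede linkage to exacerbation dates.
- **Detail may sit in the analysis plan, and the extra modelling is labelled exploratory.** This is fair for the final limit, window and resampling method. It does not answer the mismatch inside the article between a development design and the evaluation claimed in the Discussion.
- **Data collection is prospective and the laboratory work is blinded.** Both are true and are strengths. Neither makes the test of the rule prospective.
- **The article defers effectiveness to a later randomised trial.** This also stands. It does not say that the trial would rest on these sensitivity and PPV figures.

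**Conclusion.** The point holds in a limited form. As written, rules are developed and scored on the same follow-up of the same 30 people with no validation step, so sensitivity and PPV are apparent values. They are optimistic to the extent that choices are made with outcomes in view. The 24% against 14% figure shows the scale for the best of 10 rules, assuming no signal, independent windows and independent rules. It does not forecast this study's bias.

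The missing reference period is a separate uncertainty and would pull the other way: if ill days entered the limits, sensitivity would fall. In the single-parameter simulations it falls roughly threefold. With eight parameters the fall is much smaller. Every size here depends on the assumed illness length and shift, and limits based on moving ranges would be less affected by a sustained shift.

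It would go too far to say that the reported figures must be inflated overall, since the net direction is not determined by the text. What the text does support is that the Discussion's description claims more than this design can deliver. The point is worth acting on but does not undermine the study as development work.

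**What to change.** 1. State the reference period. Set each participant's limits from exacerbation-free follow-up days, freeze them, and score later periods only. Alternatively, leave out the scored period and the days around exacerbations when setting limits, which keeps more data.
2. Fix one primary limit and one primary window before linking to exacerbation dates, and label all others as secondary.
3. Put any choice of parameters, limit or model inside leave-one-participant-out cross-validation (the rule chosen on 29 and scored on the 30th, whose limits come from that person's own stable days) or bootstrap optimism correction. Report corrected sensitivity and PPV beside the apparent values.
4. Apply the exclusions of implausible values before linking to exacerbation dates.
5. In the Discussion, describe the work as model development with internal validation.

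**Cost.** This is programming and wording. The Results section places the study in data analysis, so most of it remains feasible; anything already chosen with outcomes in view should be declared and corrected for under item 3. The four stable weeks required for entry precede monitoring, so they do not make the first 28 study days clean: about 35% of participants would need a later baseline at the planning rate. On the plan's average follow-up, a 28-day baseline leaves about 276 periods against about 297 needed. Either restate the precision, or use the version in item 1 that loses fewer periods.

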**Figure 1 figure1:**
[figure not shown]
Equipment provided to participant to complete the assessments.

Each participant will be provided with a 3G-enabled tablet (iPad) and will upload peak flow, FEV_1_, pulse rate, oxygen saturation, blood pressure, temperature, and physical activity data on a daily basis. The participants will be provided with a set of instructions about uploading the data onto the iPad. The participants will be blind to their continuous data over the duration of the study but will see the values generated daily on the screens of the devices. There will be no requirement for the participant to enter numerical values into the software as all monitoring devices connect directly reducing the risk of inaccurate data entry. The data collected on the iPad is automatically transmitted to the Cloud databases. No information is stored on the iPad and if the iPad is lost, there is no risk that these data could be accessed. The company is able to track the iPad’s location in the event that it is stolen or lost.

The information uploaded by the volunteers will be remotely reviewed daily by Aseptika’s Directors to ensure that data has been uploaded on a daily basis and there are no technical problems. Technical problems will be remedied remotely by the Aseptika technical staff. In the case of information not being uploaded, Aseptika’s investigator will initially inform the research nurse who will contact the volunteer by telephone to enquire if there have been any difficulties. Should any volunteers find the technology difficult to manage, they will be offered a further home visit for instructions and training.

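### The alarm rule names no adverse direction, so read literally an unusually good reading counts as a predicted exacerbation

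*Protocol article*

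**What the plan says.** Under Analysis of Endpoints, the protocol article builds a separate chart for each participant: "Control charts will be used to determine the boundaries of normal behavior for each parameter". The first stage is to "use data on the collected parameters (eg, peak flow, pulse rate, oxygen saturation, activity data) to predict when an exacerbation is likely". The trigger follows: "When a parameter strays from normal behavior (eg, exceeds 99% control limits), an exacerbation will be predicted". The daily upload listed under Study Assessments is wider than those four examples; participants "will upload peak flow, FEV_1_, pulse rate, oxygen saturation, blood pressure, temperature, and physical activity data on a daily basis".

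Periods with and without a prediction are then compared by multilevel logistic regression, and "the sensitivity and positive predictive value of the predictions will also be calculated". The sample-size section assumes that "an exacerbation will occur in 60% of time periods in which it is predicted", that the figure is 10% in the other periods, and that a prediction is made in 1 period in 12.

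No section gives an adverse direction for any measure or sets favourable deviations aside.

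**The concern.** A control chart has a limit on each side, and the trigger is any departure from normal. For several of the measures only one side is plausibly a warning: low for peak flow, FEV1, oxygen saturation and activity, high for pulse and temperature. These directions are a reviewer's judgement; the document does not state them. Under the rule as worded, an exceptionally active day or an unusually good blow is scored like a fall.

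Taking the word for crossing a limit to mean the upper limit only does not help. High peak flow would then raise an alarm and low peak flow would not.

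The rule defines the exposure in the regression and the positive test in the sensitivity and PPV, so it bears directly on the primary objective. The Discussion also says the data will be used to identify the key elements of the system. A measure could look poor there because its good days were counted as alarms.

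**Working it through.** **1. The plan's own figures (Sampling and Sample Size).** Inputs: event rates 60% and 10%, alarms in 1 of 12 periods, 5% significance, 90% power.

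- A two-sided comparison of two proportions with continuity correction and 1:11 allocation gives 10 + 110 = 120 periods, as stated.
- Design effect: 1 + (12 − 1) × 0.18 = 2.98, taken as 3. Then 120 × 3 = 360 periods, and 360 / 12 = 30 participants, as stated.

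The calculation takes the 60%, 10% and 1-in-12 rates as given. The direction of the alarm rule does not enter it, so these numbers stand.

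**2. What those rates imply for the alarm.**

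- Periods with an event: 0.6 × 1/12 + 0.1 × 11/12 = 0.1417.
- Sensitivity: 0.0500 / 0.1417 = 0.353.
- False alarms among event-free periods: (0.4 × 1/12) / 0.8583 = 0.039.

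**3. Chance alarms, both sides against the adverse side only.** Assumptions, none of them in the document: one parameter, one independent reading a day, 10 days, and 99% limits with 0.5% in each tail.

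- Both sides: f = 1 − 0.99^10 = 0.0956.
- Adverse side only: f = 1 − 0.995^10 = 0.0489.

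With 7-day periods, the other end of the range given under Analysis of Endpoints, these become 0.068 and 0.034.

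**4. Effect on PPV.** Let s be the chance that a true warning occurs in an event period, the same under both rules; this assumes that favourable excursions carry no warning. Chance alarms in event periods also count as hits, so

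t = s + (1 − s) × f, and PPV = 0.1417t / (0.1417t + 0.8583f).

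At s = 0.353:

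- Both sides: t = 0.415; PPV = 0.0588 / (0.0588 + 0.0821) = 0.417.
- Adverse side: t = 0.385; PPV = 0.0545 / (0.0545 + 0.0420) = 0.565.

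| s | PPV, both sides | PPV, adverse side only |
|---|---|---|
| 0.353 | 0.42 | 0.56 |
| 0.60 | 0.52 | 0.68 |
| 0.90 | 0.61 | 0.75 |

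**5. Effect on the odds ratio** at s = 0.353, from [t/(1 − t)] / [f/(1 − f)]: 6.7 with both sides and 12.2 with the adverse side only. The planned rates give (0.6/0.4) / (0.1/0.9) = 13.5.

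**6. What direction does not repair.** With four such parameters, chance alarms are 1 − 0.99^40 = 33.1% with both sides and 1 − 0.995^40 = 18.2% with the adverse side only. Even the single-parameter 4.9% is above the 3.9% implied in step 2.

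**The case against.** The strongest reply is that the document never says improvements count. The 99% limit is given as an example, the article condenses a fuller protocol, and a statistical analysis plan that is not shown may set the directions. That is fair as far as it goes: a reader might infer that the study will score, or has scored, improvements as predictions, and the text does not support this. But the example covers only the threshold. The trigger itself is stated without qualification. If the analysis plan does set directions, this sentence needs to agree with it.

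Further objections that stand:

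- **The size rests on assumptions.** The document gives no standard deviations, autocorrelation or chart type. The PPV figures illustrate the effect and do not forecast it.
- **The gain depends on the tail.** A one-sided limit with a 1% adverse tail has the same 9.6% chance-alarm rate as the two-sided rule.
- **Recovery readings.** A reader might infer that direction would stop post-treatment readings being credited as predictions. That is mainly a matter of timing: an adverse reading taken after antibiotics start would be credited too.
- **Not every measure is equally exposed.** Oxygen saturation cannot exceed 100%, so its upper limit may rarely be crossed.
- **Some directions are open.** The article does not say how symptoms, wellness scores or biomarkers run.

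It is also true that this is model development, with further exploratory analysis planned and no clinical decisions resting on the data. That limits the harm but does not make the undirected rule the better choice.

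**Conclusion.** The point holds in a limited form. The stated rule has no direction, and followed literally it counts favourable excursions as predicted exacerbations. Provided such excursions do not precede exacerbations, false alarms rise, and PPV and the odds ratio would be expected to fall. In the single-parameter illustration the chance-alarm rate roughly doubles, and PPV is lower by about 0.14 to 0.15 across sensitivities of 35% to 90%.

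The documents do not support the stronger claims that the sample size is wrong, or that a directional rule would by itself restore the planned performance. Multiplicity across parameters and the timing of post-treatment readings are separate problems. The change is worth making because the rule defines the main exposure and the remedy costs almost nothing.

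**What to change.** Reword the primary rule so that an exacerbation is predicted only when a parameter crosses its limit in an adverse direction fixed before analysis, keeping the 0.5% adverse tail. Add a table of directions:

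- **Low is adverse:** peak flow, FEV1, oxygen saturation, activity.
- **High is adverse:** pulse, temperature.
- **Set by the study team, according to how each is scored:** symptom or wellness scores and sputum biomarkers.
- **No clear direction (weight, blood pressure):** keep two-sided limits and report these alarms separately.

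Move other two-sided signals to the exploratory analysis already planned. The cost is one table and one reworded sentence, with no new data and no change to the 360 periods. The small downside is that an unexpected signal on the favourable side would appear only in the exploratory results.

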#### Study Assessments

Participants will be asked to undertake the following once a day every day during a 6-month follow-up period, with assistance from carers as appropriate. Figure 1 illustrates the equipment that will be provided to the participant to facilitate these assessments.

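### If any of four or more daily parameters can raise the alarm at 99% limits, chance alarms far exceed what the sample size assumes

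*Protocol article*

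**What the plan says.** Under Analysis of Endpoints, each participant gets a separate control chart for each parameter, and "When a parameter strays from normal behavior (eg, exceeds 99% control limits), an exacerbation will be predicted". The parameters are introduced as "collected parameters (eg, peak flow, pulse rate, oxygen saturation, activity data"), so four are named as examples. For the comparison with actual exacerbations, "participant follow-up will be divided into periods of time (eg, 7-10 days"). The section states no rule for combining parameters, no direction for the limits and no false-alarm rate per period.

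Under Study Assessments, measurements are taken "once a day every day during a 6-month follow-up period", and each participant "will upload peak flow, FEV_1_, pulse rate, oxygen saturation, blood pressure, temperature, and physical activity data on a daily basis". That is seven device measures, or eight if systolic and diastolic pressure are counted apart. Adding weight or symptoms makes nine or more.

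Under Sampling and Sample Size, "Time periods will consist of approximately 10 days". An exacerbation is expected in 60% of periods with a prediction and 10% of those without. "It is also assumed that a predicted exacerbation will be made in only 1 in 12 time points (8% of all time points"). That section ties these figures to prediction from sputum biomarkers; the Introduction allows 1 to 3 of them.

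**The concern.** A 99% limit lets through about 1% of readings by chance. A period of 7-10 days holds many readings, and more still if several parameters each have their own chart. If one excursion on one chart is enough to call the period predicted, the predicted group fills with chance alarms.

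The prediction indicator is the exposure in the multilevel logistic regression and the basis of the reported sensitivity and PPV. Excess chance alarms pull the odds ratio toward 1 and the PPV toward the base rate, so a useful marker could look weak because of the alarm rule. The sample size would also describe a much more selective alarm than the one analysed.

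**Working it through.** **1. The plan's own figures.** Inputs from Sampling and Sample Size: 60% against 10%, a 1:11 split of predicted to unpredicted periods, 5% significance, 90% power. Two-sided testing is assumed, as sidedness is not stated. The two-proportion formula gives 7.31 predicted periods, or 9.37 with continuity correction. Rounding up to 10 gives 10 × 12 = 120 periods (96 without the correction). Design effect 1 + (12 − 1) × 0.18 = 2.98; 120 × 2.98 = 358, about 360; 360/12 = 30 participants. All three figures reproduce.

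**2. What those figures imply about the alarm.**
- Base rate P = 0.6/12 + 0.1 × 11/12 = 14.2% of periods.
- Sensitivity = (0.6/12)/0.1417 = 35%.
- False-alarm rate in stable periods = (0.4/12)/(1 − 0.1417) = 3.9%.
- Largest false-alarm rate compatible with a PPV of 60% at 100% sensitivity = 0.1417 × (0.4/0.6)/0.8583 = 11.0%.

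**3. What the 99% rule gives by chance.** Assumptions: 1% of stable readings fall outside the limits, one excursion on any counted parameter flags the period, and readings are independent. For k parameters over L days, f = 1 − 0.99^(kL). Highest PPV (100% sensitivity) = P/(P + f(1 − P)).

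| k | f, 10 days | Max PPV | f, 7 days | Max PPV |
|---|---|---|---|---|
| 1 | 9.6% | 63.3% | 6.8% | 70.8% |
| 3 | 26.0% | 38.8% | 19.0% | 46.5% |
| 4 | 33.1% | 33.3% | 24.5% | 40.2% |
| 7 | 50.5% | 24.6% | 38.9% | 29.8% |
| 9 | 59.5% | 21.7% | 46.9% | 26.0% |

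**4. Correlated readings.** The article gives no correlations, so these are assumed: normal data, first-order autoregressive over days, equal correlation between parameters, by simulation. Ranges cover 4-9 parameters and 7-10 days.

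| Day-to-day / between-parameter correlation | f | Max PPV |
|---|---|---|
| 0.5 / 0.3 | 22-52% | 24-43% |
| 0.8 / 0.3 | 17-41% | 29-50% |
| 0.9 / 0.5 | 11-26% | 39-59% |

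With four or more parameters the ceiling stays below 60% throughout, though only just in the most favourable corner (four parameters, 7 days, strong correlation: 59%).

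**5. One biomarker, as in the sample-size section (10 days, independent readings).** Chance alarms take 0.096 × 0.858 = 8.2% of all periods, against 8.3% assumed for true and false alarms together. A PPV of 60% needs sensitivity × 0.1417 = 1.5 × 0.082, so sensitivity = 87%. The share of periods flagged would then be 0.87 × 0.142 + 0.082 = about 20%. At the implied 35% sensitivity the PPV would be about 38%.

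**6. Power for the association (120 effective periods, f = 33%).** About 4% at 35% sensitivity, 81% at 70% and 99% at 90%.

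**The case against.** The text says a parameter, not any parameter. It could mean that each parameter is assessed on its own, which would suit the aim in the Discussion of finding the key elements of the system. It also does not say that one reading flags a whole period. The 99% limit, the parameter list and the 7-10 days are all examples, and a separate analysis plan may settle the rest. The planning figures belong to the sputum biomarkers, while the parameters named in the analysis section are telemetry.

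Most of this stands. A reader might infer that the alarm will fire in 30-60% of stable periods, that 60% PPV is out of reach, or that the two sections are irreconcilable. The article does not support these as general statements: they depend on four or more parameters feeding one alarm at 99% limits, and the upper figures also on near-independence. One biomarker could reach 60% at high sensitivity. With day-to-day correlation of 0.9, its simulated chance-alarm rate is 3.5-4.7%, close to the implied 3.9%. Three independent biomarkers, however, give 19-26%.

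Nor does the material show that the study is underpowered. Low PPV is not low power, and power depends on an unknown sensitivity. Because sensitivity and PPV are to be reported with confidence intervals, many false alarms would show up as a low PPV.

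One part of the objection fails. This is not a complaint about missing detail: the article states a trigger and states operating figures, and on a natural reading they do not fit. Loosening the example does not settle it either. At 3-sigma limits, seven independent parameters over 10 days still give 17% chance alarms and a PPV of at most 49%.

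**Conclusion.** The concern holds conditionally. If any of four or more daily parameters can raise the alarm at 99% limits, chance flags about 33-60% of stable 10-day periods with 4-9 independent parameters, 25-47% over 7 days, and about 11-26% under strong assumed correlation. The planning figures allow 3.9%. Under that reading the PPV stays below 60% even with perfect sensitivity.

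For a single daily biomarker the mismatch is smaller but present if readings are independent: chance alarms alone nearly use up the 8% of periods, and 60% PPV requires about 87% sensitivity with about 20% of periods flagged. Strong day-to-day correlation would narrow this gap.

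The sample-size arithmetic is correct; what is in doubt is whether its inputs describe the stated alarm. The result rests on the any-parameter reading, a 1% chance excursion per reading, the 14.2% base rate implied by the plan, and correlations that the article does not give.

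**What to change.** Change the analysis wording as follows:

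- Name the sputum-biomarker alarm as the primary predictor, in line with Sampling and Sample Size. Evaluate telemetry parameters separately or through one combined alarm.
- Use limits in the direction of deterioration, so that an unusually good reading does not count as a prediction.
- Fix the total chance-alarm rate per period in advance, calibrated on stable days, through Bonferroni-type limits or a persistence rule. As a guide for independent readings over 10 days, 4-9 parameters need limits of about 99.7% to 99.87% to bring the rate to 11%, and about 99.90% to 99.96% to bring it to 3.9%.
- Report the false-alarm rate beside sensitivity and PPV.
- Restate the 8% and 60% to match the chosen rule.

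The Results section says the study is already in data analysis, so the change should be documented and justified under the article's procedure for deviations from the statistical analysis.

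No new data are needed. The cost is that tighter limits or persistence lower sensitivity to isolated one-day excursions. A multivariate chart such as Hotelling T2 or MEWMA is optional: it needs complete daily vectors, and the missing-data section rules out imputation in the primary analysis.
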